### Statistical analyses

According to the principle of intention-to-treat, all randomized participants will be analyzed using SPSS version 18.0 (SPSS Inc., Chicago, IL, USA) software. All data will be represented as mean ± standard deviation (SD) or number (%). For comparisons of two groups, an independent samples *t*-test or Mann- Whitney *U* test will be used for continuous outcomes, and a χ^2^-test or Fisher’s exact test will be used for noncontinuous outcomes. To control for possible confounding factors (for example, age, Hunt and Hess Scale, modified Rankin Scale, *etcetera*), multiple regression analysis will be performed for the comparison of two groups. Confidence limits of 95% will be calculated and *P* values of < 0.05 will be considered statistically significant.

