### Participants

#### Subject enrollment, randomization, and blinding

A total of 80 participants will be recruited for this trial. Patients with SAH admitted to our hospital are potential candidates for the study. Eligible participants will be randomized to the study group or the control group after written informed consent is obtained. Concealed allocation will be achieved by randomization and allocation by an assigned researcher without patient contact. Randomization will be done using a computer-generated allocation list by an assigned researcher not involved in the intervention or assessment. Stratified block randomization will be carried out according to sex and the Hunt and Hess Scale (HHS) [25]. The physician involved in the intervention will receive a random number by phone after the informed consent form has been signed and the HHS has been evaluated. A flow chart of the study is presented in Figure 1.

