### Sample size estimation

DIND, the primary outcome of the trial, was used to calculate the sample size. According to our pilot trial carried out in 2012, the incidence rate of DIND was 10% in the study group and 38.9% in the control group [24]. The difference in the expected incidence rate of DIND between the two groups (P_c_ - P_t_) is therefore 28.9%. To detect this difference with a two-sided 5% significance level and a power of 95%, 39 participants per intervention arm have to be randomized, allowing for a 20% dropout rate [31].$$ n=\frac{{\left({z}_{\alpha /2}+{z}_{\beta}\right)}^2\left({p}_c{q}_c+{p}_t{q}_t\right)}{{\left({p}_c-{p}_t\right)}^2} $$

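### The test rule has no class for ordinal outcomes, so read literally it gives the mRS score a test that ignores the order of its grades

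*Protocol article*

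**What the plan says.** The Statistical analyses section of the protocol article assigns tests by type of outcome only:

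- Continuous: "an independent samples *t*-test or Mann- Whitney *U* test will be used for continuous outcomes".
- Everything else: a chi-square or Fisher's "exact test will be used for noncontinuous outcomes".

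There is no third class for ordered categories, and the rule does not name the mRS. On presentation the section says: "All data will be represented as mean ± standard deviation (SD) or number" (with percentage), which offers no ordinal summary. It adds that, to control for confounders, "multiple regression analysis will be performed for the comparison of two groups". The type of regression is not given, and the mRS appears there only as an example of a confounder. Confidence limits of 95% are planned.

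The section Secondary outcome measurements lists the mRS score as the measure of functional status, at the end of treatment and 14 days later (or at discharge). It sets no cut-point and no separate test.

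**The concern.** Noncontinuous is the complement of continuous, so by its wording the second class takes in ordered scales as well as binary outcomes. The mRS is an ordered scale. Under that reading its grades are compared as unrelated labels in a table of up to 2 × 7. Such a test gives the same result if the grades are shuffled, so it cannot use the fact that one arm lies consistently toward the better end. It also yields no single effect measure.

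The rank test that would use the order is named only for the other class. If the analyst instead treats the score as continuous, the text allows either a t-test or Mann-Whitney. More than one analysis of the functional outcome could then be defended after the data are known.

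**Working it through.** **1. Is there a figure in the plan to reproduce?** Not for the mRS: no distribution, effect size or power is stated. The only sample-size figure is 39 per arm for DIND. It is a separate matter and serves here only to set the scale. The printed formula with 38.9% and 10% gives

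n = (z_α/2 + z_β)² × (0.389 × 0.611 + 0.10 × 0.90) / 0.289² = (z_α/2 + z_β)² × 0.3277 / 0.0835.

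At 95% power this is 50.98, so 51, and 51/0.8 gives 64 after dropout. At 80% power it is 30.79, so 31, and 31/0.8 gives 39. The stated 39 therefore fits 80% power and not the stated 95%. Nothing below depends on this.

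**2. Inputs for the power comparison.**

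- From the protocol: "A total of 80 participants will be recruited for this trial", hence 40 per arm with equal allocation. With the 20% dropout in Sample size estimation, 40 × 0.8 = 32 per arm. Two-sided 5% level.
- Assumed, because the documents give nothing: seven mRS grades compared without collapsing; four control distributions over grades 0 to 6, namely flat, skewed to good outcome (20/22/16/12/12/8/10%), severe (4/8/12/16/22/24/14%) and U-shaped (22/16/10/8/10/12/22%); and a uniform shift with common odds ratio (OR) from 1.5 to 5.

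**3. Model.** For each grade j below the worst, logit P(mRS ≤ j | acupuncture) = logit P(mRS ≤ j | control) + ln(OR). There were 6,000 simulated trials per setting, each tested by Pearson chi-square on the full table and by tie-corrected Mann-Whitney.

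**4. Results at 40 per arm** (range over the four distributions; relative loss = 1 − chi-square power / Mann-Whitney power):

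| Common OR | Chi-square | Mann-Whitney | Relative loss |
|---|---|---|---|
| 1.5 | 0.08–0.09 | 0.17 | 49–56% |
| 2 | 0.19–0.20 | 0.41–0.42 | 52–56% |
| 2.5 | 0.31–0.34 | 0.62–0.63 | 47–50% |
| 3 | 0.46–0.48 | 0.77–0.79 | 38–41% |
| 4 | 0.68–0.71 | 0.92–0.94 | 23–26% |
| 5 | 0.83–0.85 | 0.97–0.98 | 14–15% |

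At 32 per arm the loss is 53–59% at OR 2, 45–48% at OR 3 and 22–25% at OR 5. With no effect, both tests reject in about 4 to 5% of trials, so the gap is not due to a difference in error rate.

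**5. Analytic cross-check.** Under a uniform shift nearly all the signal lies in one direction, but the unordered test spreads it over 6 degrees of freedom. In the noncentral chi-square approximation, an effect with 80% power on 1 df has 52% on 6 df (relative loss 35%), and one with 50% has 26% (48%). This agrees with the simulation.

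**6. Where the ranking reverses.** Take control proportions 20:22:16:12:12:8:12 (rescaled to sum to one) and treated proportions 20/22/30/12/4/2/10%, so that patients move mainly from grades 4 and 5 to grade 2. At 40 per arm chi-square then has power 0.27 and Mann-Whitney 0.12. The advantage of the rank test depends on the shift running along the whole scale.

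**The case against.** The strongest objection is that the protocol never assigns the mRS to chi-square. It calls it a score, and with only two classes available many analysts would put a scored scale with the numeric outcomes, where Mann-Whitney is already allowed. This stands in part. A reader might infer that the plan commits the mRS to an unordered test; the text does not say so. It says that noncontinuous outcomes get one, and the literal reading puts an ordered scale there.

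A second objection is that the test for one secondary outcome is a detail for the analysis plan, which is not shown. That would hold if the article were silent. It is not silent: it states a rule covering all outcomes, and that rule handles an ordered one badly.

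A third is that the plan also contains a multiple regression and 95% confidence limits. This is correct. A reader might infer that the mRS would be left with a bare P value and no effect estimate; the planned regression rules out that conclusion. Its model type is not stated, however, so it does not show that the order of the grades would be used.

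A fourth is that a flat claim of half the power lost would be too strong. This also stands. The figure holds only for small to moderate assumed shifts, and the ranking can reverse.

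**Conclusion.** The point holds in a limited form. The stated rule lacks an ordinal class. Its literal wording points the mRS to a test that ignores order, while a looser reading permits Mann-Whitney or a t-test. The power cost of the literal reading at 40 per arm is roughly half for common odds ratios of 1.5 to 2.5, about 40% at 3 and about 15% at 5, and somewhat larger at 32 per arm. These figures rest on seven uncollapsed grades, assumed control distributions and a uniform shift; none comes from the documents. The mRS is secondary. The primary outcome, DIND, is binary, so chi-square or Fisher's exact suits it, and neither its analysis nor the sample size is touched by this point. A change is advisable because it is cheap and the mRS is the only functional-status outcome.

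**What to change.** Amend Statistical analyses to say three things:

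- The mRS is compared at each of the two time points by proportional-odds (ordinal logistic) regression with arm, HHS, sex and baseline mRS, reporting the common odds ratio with its 95% CI.
- Mann-Whitney U is the unadjusted check.
- Chi-square and Fisher's exact are limited to binary outcomes.

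HHS and sex are the stratification factors and baseline mRS is already assessed, so no new data are needed. The cost is a wording change; SPSS fits the model. The downside is the proportional-odds assumption, which matters if the effect is not a uniform shift. Mann-Whitney does not require that model, but it too is weak against effects confined to part of the scale, so the full distribution of grades by arm should be shown alongside.

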### Outcome measures

#### Primary outcome measurement

The occurrence of DIND will be compared between the study group and the control group. DIND is defined as an unaccountable new focal neurological deficit lasting ≥2 h. Any occurrence of DIND will be recorded by the physician and verified by the investigator every day.

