## Discussion

In this randomized controlled trial, we aim to observe the effect of acupuncture treatment on the prevention of vasospasm after SAH. In addition to the occurrence of DIND and vasospasm, plasma levels of NO and endothelin-1 will be evaluated to identify the mechanism of action of the treatments used. Stratified block randomization will be used according to sex and severity (HHS). For the placebo control, we will use an electric stimulator without electrical flow and sham intradermal acupuncture designed not to penetrate the skin. With use of the same electrical stimulator and intradermal acupuncture method as the treatment group, better blinding of the control group is expected. Participants will be treated alone in a treatment room in order to avoid any communication with other participants.

In summary, the effect of acupuncture treatment on the prevention of vasospasm after SAH will be assessed in this trial. The placebo effect should be excluded and the trial design should allow for evaluation of the efficacy and safety of acupuncture for SAH patients.

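### The test stated for DIND does not use the randomization strata, and the adjusted comparison has an open covariate list and no stated rank

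*Protocol article*

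**What the plan says.** On allocation, the protocol article (Subject enrollment, randomization, and blinding) states: "Stratified block randomization will be carried out according to sex and the Hunt and Hess Scale (HHS"). The Discussion repeats the same two factors. The eligible HHS grades are 1 to 4. The article does not say whether grades are grouped for the randomization.

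On the primary outcome (Primary outcome measurement): "The occurrence of DIND will be compared between the study group and the control group". This is a yes/no outcome.

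On analysis (Statistical analyses), a chi-square or Fisher's "exact test will be used for noncontinuous outcomes", with no mention of strata. To control for possible confounders, the section adds that "multiple regression analysis will be performed for the comparison of two groups". The confounders are introduced as "for example, age, Hunt and Hess Scale, modified Rankin Scale", and the list then ends in an et cetera. One threshold, P < 0.05, covers everything. No sentence says which of the two comparisons decides the trial.

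**The concern.** If sex and HHS matter enough to stratify on, the analysis should normally use them. Stratified blocks make the arms more alike than simple randomization would. A test that ignores this overstates the variance of the difference, so it rejects too rarely and gives up some power.

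The second issue is freedom of choice. Two comparisons of the same outcome stand side by side, unranked, and one has a covariate list without an end. With few events, the fitted effect can shift with the covariates chosen, and nothing in the published text stops that choice from being made once the data are seen.

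**Working it through.** **Inputs from the article.** DIND 38.9% (control) and 10% (study); 80 participants, taken as 40 per arm; two-sided 5%; strata sex × HHS, at most 2 × 4 = 8, or 10 participants per stratum on average. The article gives no stratum-specific risks, stratum mix or block size, so these are assumptions below. It states no figure on this point that could be reproduced.

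**1. Expected events.** 40 × 0.389 + 40 × 0.10 = 15.6 + 4.0 = 19.6. With 31 analysed per arm after 20% dropout: 31 × 0.489 = 15.2. A model with treatment, age, HHS, mRS and sex as single terms has five parameters: 19.6/5 = 3.9 or 15.2/5 = 3.0 events each.

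**2. Null rejection of the unstratified test.** Take four equal strata with arms balanced in each. The chi-square test uses the variance p̄(1−p̄). The variance that applies is the mean of p(1−p) within strata.
- Control risks 10/25/50/70%: p̄ = 0.3875 and p̄(1−p̄) = 0.2373. The within-stratum mean is (0.09 + 0.1875 + 0.25 + 0.21)/4 = 0.1844. The ratio is 0.777, and its square root 0.881. The effective cut-off is 1.96/0.881 = 2.22, so the rejection rate is about 2.6%.
- Control risks 20/30/45/60%: the within-stratum mean is (0.16 + 0.21 + 0.2475 + 0.24)/4 = 0.2144. The ratio is 0.903, the cut-off 1.96/0.950 = 2.06, and the rejection rate about 3.9%.
- Equal risks: the ratio is 1 and the rate 5%.

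**3. Power, calibrated to the planned rates.** The marginal odds ratio is (0.10/0.90)/(0.389/0.611) = 0.175. It must not be applied unchanged inside prognostic strata: with risks of 10–70% it leaves a mean treated risk of 12.8%. The within-stratum odds ratio has to be set so that the treated mean is 10%. Simulation (200,000 trials per row, 10 per arm in each stratum):

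| Control risks | Within-stratum odds ratio | Null rejection, chi-square v Mantel-Haenszel | Power, chi-square v Mantel-Haenszel |
|---|---|---|---|
| 10/25/50/70% | 0.129 | 2.6% v 4.9% | 89.8% v 92.4% |
| 20/30/45/60% | 0.155 | 4.0% v 4.8% | 88.7% v 89.8% |
| 38.9% in all | 0.175 | 5.0% v 5.1% | 88.2% v 88.2% |

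With 20/33/47/60% the null rate of the chi-square test is 4.1%. That these powers fall below the 95% in the plan is a separate matter of sample size.

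**4. Sparser strata.** Eight strata, blocks of four, odds ratios of 1 to 3 per HHS grade and 1 to 1.5 for sex (4,000 trials per setting):
- Null rejection: 3.3–5.5% (chi-square) v 4.7–5.3% (Mantel-Haenszel).
- Power with 80 analysed: 88–90% v 87–92%.
- Power with 64 analysed: 80–81% v 78–84%.
- At the non-prognostic end, Mantel-Haenszel is about one point worse with 80 analysed (87.2% v 88.4%).

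**5. Choosing among models.** Age, HHS, mRS and sex give 2⁴ − 1 = 15 covariate sets. In null trials of 80 (2,500 per scenario, mild to strong assumed covariate effects), each analysis fixed in advance rejected in about 2.8–6.0%. Taking the smallest p-value among the chi-square test and the 15 logistic models rejected in about 6.4–9.2%.

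**The case against.** The case for leaving the text alone is substantial, and most of it stands.

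- **An unstratified test after stratified randomization is valid.** A reader might infer that it produces false positives. It does not: at worst it is conservative, and only if the strata predict DIND. The article gives no data on that.
- **The plan does not ignore severity.** HHS is named in the adjusted comparison. A reader might infer that sex is excluded, but the list is illustrative. Sex is unnamed, not ruled out.
- **The regression need not be linear.** A reader might infer that a linear model will be fitted to DIND. The sentence covers all outcomes, including NO and endothelin-1, and the term can include logistic regression. The text supports only that no model for a binary outcome is specified.
- **There is a natural reading of rank.** The simple test comes first, the regression follows with a stated purpose of confounder control, and the sample-size formula is an unadjusted comparison of two proportions. This makes unadjusted main and adjusted supportive the likelier intent, but no sentence says so.
- **A larger power loss can be simulated** (about 80% v 84%), but only by applying the marginal odds ratio of 0.175 within strata. That no longer matches the planned 10%.
- **A full analysis plan may settle the details.** Missing detail is therefore not the complaint. The complaint is what the article does state: a test without strata and a covariate list written as open.

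**Conclusion.** The point holds in a limited form. The stated DIND test does not match the stratified design, and the adjusted comparison is loosely fixed: open list, sex not named, no binary model, no rank.

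The cost of ignoring the strata is small and in the conservative direction: null rejection of about 2.6–4.1% instead of 5%, and about 1–3 points of power under the assumed risks of 10–70% or 20–60% in four equal strata. It is nil if the strata are not prognostic. The loose covariate rule matters more. With about 20 events, picking among plausible models could raise the false-positive rate to roughly 6–9% under the assumptions shown. That measures what the wording permits and does not show that anyone intends it. The validity of the trial is not in question. The change is worth making because it is almost free.

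**What to change.** In the Statistical analyses section:

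1. Name one primary analysis of DIND: a Mantel-Haenszel test stratified by sex and HHS as grouped in the randomization, with a stratified risk difference and 95% CI. State in advance how HHS grades will be pooled if strata are sparse.
2. Label the unadjusted chi-square or Fisher's exact test as a sensitivity analysis.
3. Delete the et cetera. Label any further covariate model as supportive, logistic for DIND, with a short closed list suited to 15 to 20 events.

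The cost is analysis wording only, with no new data, visits or participants. It should be fixed before unblinding. The downside is that eight strata in 80 participants may be sparse, and if the strata are only weakly prognostic the gain is negligible, or a loss of about a point of power.

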## Discussion

In this randomized controlled trial, we aim to observe the effect of acupuncture treatment on the prevention of vasospasm after SAH. In addition to the occurrence of DIND and vasospasm, plasma levels of NO and endothelin-1 will be evaluated to identify the mechanism of action of the treatments used. Stratified block randomization will be used according to sex and severity (HHS). For the placebo control, we will use an electric stimulator without electrical flow and sham intradermal acupuncture designed not to penetrate the skin. With use of the same electrical stimulator and intradermal acupuncture method as the treatment group, better blinding of the control group is expected. Participants will be treated alone in a treatment room in order to avoid any communication with other participants.

In summary, the effect of acupuncture treatment on the prevention of vasospasm after SAH will be assessed in this trial. The placebo effect should be excluded and the trial design should allow for evaluation of the efficacy and safety of acupuncture for SAH patients.

### Trial status

Recruitment started in September 2014 and will be completed by the end of May 2016.

## Abbreviations

CT: Computed tomography
DIND: Delayed ischemic neurological deficit
FG: Fisher grade
HHS: Hunt and Hess Scale
MRI: Magnetic resonance imaging
mRS: Modified Rankin Scale
NO: Nitric oxide
SAH: Subarachnoid hemorrhage
TCD: Transcranial doppler
triple-H: Hypertensive, hypervolemic, and hemodilution
